### Study groups

2.6

Participants are randomly assigned to one of six groups (arms) in a 1:1:1:1:1:1 ratio. Four groups are primary comparison arms for the main efficacy analysis at 6 weeks, and two additional groups are included for secondary analyses of conditioned stimulus specificity in Phase 2.

**Group 1: Hypnosis** + **Essential Oil (Bergamot).** Participants receive the self-hypnosis audio and inhale bergamot essential oil during each session in Phase 1. In Phase 2, they continue with bergamot oil only (no audio) on the same schedule. This is a conditioned stimulus (CS)-match condition where the same essential oil is used for conditioning and testing.

**Group 2: Hypnosis** + **Essential Oil (Lavender).** Participants receive the hypnosis audio plus lavender essential oil inhalation during Phase 1 sessions. In Phase 2, they use lavender oil only without hypnosis. This is the CS-match for lavender.

**Group 3: Hypnosis Only (No Oil).** Participants receive guided hypnosis sessions in Phase 1 with no aromatherapy. This controls for the effects of hypnosis alone. They do not use any aroma in Phase 2 either and effectively have no active intervention in weeks 7–8.

**Group 4: Minimal Intervention Control.** Participants do neither hypnosis nor essential oil in Phase 1. Instead, they may receive a minimal activity just to match time/expectation. This arm serves as a baseline and expectancy control. They also do not receive any aroma in Phase 2.

**Group 5: Hypnosis** + **Oil (Bergamot) → Switch to Lavender.** These participants start identical to Group 1 (hypnosis + bergamot oil in Phase 1). However, in Phase 2 they experience a CS-mismatch by switching to lavender without hypnosis. This group helps test if a different scent can trigger relaxation or if the effect is lost when the conditioned stimulus changes. It serves as a control for Group 1 in the conditioning analysis.

**Group 6: Hypnosis** + **Oil (Lavender) → Switch to Bergamot.** These participants mirror Group 2 initially (hypnosis + lavender in Phase 1), then switch to bergamot oil only in Phase 2, creating a CS-mismatch. This serves as a control for Group 2 to assess stimulus specificity.

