**Week 6: Post-Intervention Assessment (T1).** At the end of week 6, after the last Phase 1 session, all participants complete the T1 online survey. This repeats the same set of standardized questionnaires as at baseline (MDBF Calmness-Restlessness, GAD-7, PSS-14, PSQI, WHO-5, PSWQ) to quantify changes in relaxation and secondary outcomes from T0 to T1. In addition, participants are asked an open-ended question about their experience by asking for example, “Please describe how you experienced the intervention.” and “How did you integrate the intervention into your daily life?” This qualitative prompt allows them to reflect on any perceived benefits, challenges, or routine they developed over the six weeks. The responses, entered as free text, will later be analyzed to gain insights into engagement, acceptability, and subjective impact. This approach further allows for the identification of unforeseen themes that may emerge in connection with the intervention. Participants in the physiology subgroup come into the lab around this time for their second physiological measurement.

**Weeks 7–8: Conditioning Phase 2.** These two weeks focus on testing conditioned relaxation. Participants in Groups 1, 2, 5, 6 now use the aroma stick alone every two days, without using the hypnosis audio. Group 1 continues with bergamot essential oil inhalation; Group 2 with lavender oil, both maintaining the same CS as in conditioning (match). Group 5 switches to lavender oil only, after being conditioned with bergamot, and Group 6 switches to bergamot oil only, after conditioning with lavender. Group 3 and Group 4 will not be followed up in this phase. As in Phase 1, participants in the active arms (1, 2, 5, 6) will record a VAS relaxation rating before and after each aroma exposure to quantify any immediate relaxation effect from the scent. This data will show whether merely inhaling the familiar essential oil produces a significant calmness boost, and whether that holds true only for the matching scent or also occurs with a mismatched scent).

**Week 8: Final Assessment (T2).** At the end of week 8, all participants, including groups 3 and 4, complete a T2 survey which again includes the MDBF Calmness-Restlessness subscale and the secondary outcome questionnaires (GAD-7, PSS-14, PSQI, WHO-5, PSWQ). This final measurement captures any further changes after the Phase 2 period.

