In addition to these standardized measures, intervention adherence and acceptance will be evaluated through a custom questionnaire at T1. This includes items about how often participants actually used the intervention as instructed (adherence), how easy or practical it was to integrate into daily life, any barriers encountered, and subjective perceived benefit or satisfaction with the intervention. These data will be reported descriptively to assess feasibility and user acceptance of this digital self-help approach. There is also an exploratory “worry context” checklist module: participants indicate the domains of life in which they currently experience the most worry such as work, relationships, health, and finances. While not an outcome *per se*, this can help describe the sample and potentially stratify whether the intervention effects differ by worry context.

From the Phase 2 conditioning period, the primary outcomes of interest remain subjective relaxation (MDBF Calmness) and VAS relaxation ratings. The critical comparison here is between matched vs. mismatched scent groups. If classical conditioning is successful and stimulus-specific, Groups 1 and 2, who get the same essential oil in Phase 2 as they had during conditioning, should show a greater relaxation response than Groups 5 and 6, who receive a different scent in Phase 2. In contrast, if any scent simply produces a general context effect, the mismatch groups might also relax, suggesting a more generalization or context effect rather than a specific conditioned link. Group 3 (hypnosis only) and Group 4 (minimal control) provide additional reference points at T2 such as Group 3 might show if any residual benefit of hypnosis persists without further sessions, and Group 4 indicates any natural change over 8 weeks without intervention.

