### Hypotheses

2.10

**Primary Hypothesis (H1—Efficacy).** After six weeks of intervention (T1), participants receiving self-hypnosis combined with essential oil inhalation (Groups 1 and 2) will demonstrate greater improvement in subjective relaxation, as measured by the Multidimensional Mood Questionnaire (MDBF), compared to participants receiving self-hypnosis without essential oil (Group 3) or a minimal-intervention control (Group 4).

**Primary Null Hypothesis (H0).** There are no differences between intervention groups in change in subjective relaxation from baseline to T1. **Primary Alternative Hypothesis (H1).** At least one intervention group differs from the others with respect to change in subjective relaxation from baseline to T1.

**Secondary Hypothesis 2.1 (Conditioned Relaxation).** In Phase 2, the essential oil alone will elicit relaxation in those groups that have consistent pairing in Phase 1. Specifically, participants in the CS-match conditions (Group 1 with bergamot, Group 2 with lavender) will show a significant increase in relaxation as measured by pre-post VAS and possibly MDBF from T1 to T2, when exposed to the essential oil alone, whereas those in CS-mismatch conditions (Group 5 and 6, who receive a different oil than used in training) will have smaller or no relaxation response. We hypothesize a stimulus-specific conditioning effect, meaning the relaxation response is tied to the particular essential oil used during training, not just any pleasant essential oil.

**Secondary Hypothesis 2.2 (Broader Psychometric Benefits).** The combined hypnosis + essential oil intervention will lead to greater improvements in other psychological outcomes compared to hypnosis alone or minimal intervention. We expect to see reductions in self-reported anxiety symptoms (lower GAD-7 scores), perceived stress (lower PSS-14), and worry (lower PSWQ-d) as well as improvements in sleep quality (lower PSQI) and overall well-being (higher WHO-5) in Groups 1 and 2 vs. Groups 3 and 4 at T1. This hypothesis posits that beyond immediate relaxation, the 6-week intervention confers broader mental health benefits (less anxiety and stress, better sleep and mood), echoing findings that combined mind-body interventions can positively affect multiple domains of functioning.

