### Data analysis

2.13

The primary outcome (MDBF calmness subscale change from T0 to T1) will be analyzed using an ANCOVA model. The model will include the study group (4 arms for primary analysis: Groups 1–4) as the independent variable and the baseline MDBF score as a covariate to control for any initial differences and improve statistical power. This aligns with the principle of analyzing covariance to account for baseline variance. The primary contrast of interest is whether either of the two combination groups (1: Hypnosis + Bergamot, 2: Hypnosis + Lavender) differ significantly from the control groups (3: Hypnosis-only, 4: Minimal intervention) in adjusted mean relaxation at T1. We anticipate a significant overall group effect; planned pairwise comparisons with appropriate correction for multiple comparisons, if needed, will examine specific differences, especially 1 vs. 3, 2 vs. 3, and combined 1&2 vs. combined 3&4. The primary hypothesis will be supported if Groups 1 and 2 show statistically greater increases in relaxation than Group 3 and Group 4 (*p* < .05, two-tailed).

For Phase 2 conditioning effects, a similar ANCOVA or mixed-model approach will be used at T2. The analysis will focus on the four groups that underwent Phase 2 aroma testing (Groups 1, 2 with match vs. Groups 5, 6 with mismatch). We will compare relaxation outcomes at T2 among these, using T1 values as covariates. A significant difference (e.g., match > mismatch) on the MDBF relaxation change from T1 to T2 or on the Phase 2 VAS responses would support H2.1. We may also use repeated measurements ANOVA or multilevel modeling incorporating all three time points (T0, T1, T2) to examine group × time interactions across the full study duration. The VAS data from each session will be analyzed using linear mixed-effects models, which can handle multiple observations per participant. These models will test differences in immediate relaxation gain per session by group and can also model time trends (session number as a predictor) to see if there is a significant upward trend in pre-session relaxation over the 6 weeks for each group (learning effect).

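### With no scent-free Phase 2 session and no oil arm without prior conditioning, within-arm VAS gains and equal match/mismatch gains cannot be credited to scent or generalisation

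*Protocol article*

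**What the plan says.** **Who is exposed and rated.** Section 2.7 states "Participants in Groups 1, 2, 5, 6 now use the aroma stick alone every two days, without using the hypnosis audio", and that "participants in the active arms (1, 2, 5, 6) will record a VAS relaxation rating before and after each aroma exposure". Groups 1 and 2 keep their Phase 1 oil. Group 5 goes from bergamot to lavender and Group 6 from lavender to bergamot. All four had six weeks of hypnosis paired with an oil (2.6).

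**Who is not.** Of the other two arms 2.7 says "Group 3 and Group 4 will not be followed up in this phase". Of Group 3, 2.6 says "They do not use any aroma in Phase 2 either and effectively have no active intervention in weeks 7–8". Group 4 has no aroma either. Both complete the T2 questionnaires, which 2.9 treats as reference points.

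**What is claimed.** On the session ratings, 2.7 says "This data will show whether merely inhaling the familiar essential oil produces a significant calmness boost". Section 2.5.1 likewise presents them as capturing relaxation due to scent alone. Hypothesis 2.1 opens with "In Phase 2, the essential oil alone will elicit relaxation in those groups that have consistent pairing in Phase 1" and predicts a significant pre-post VAS increase in the match arms. If the mismatch arms relax too, 2.9 offers this reading: "the mismatch groups might also relax, suggesting a more generalization or context effect rather than a specific conditioned link".

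**What decides H2.1.** Section 2.9 calls match versus mismatch the critical comparison. Section 2.13 takes a difference between these groups, on MDBF change from T1 to T2 or on Phase 2 VAS, as support. It does not say whether the contrast is pooled over oils or adjusted for the Phase 2 oil. Section 2.6 names Group 5 as the control for Group 1 and Group 6 as the control for Group 2.

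**The concern.** Hypothesis 2.1 has two parts: that the oil alone elicits relaxation, and that this is specific to the trained oil. Match versus mismatch addresses the second. The first is phrased as a change within arms, and the design has no comparator for it.

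A Phase 2 session is several minutes of inhaling, after six weeks of relaxation training, by participants who know that they are using an oil. Some pre-post gain could arise from pausing, from expecting to relax, or from the oil itself, which the Introduction describes as anxiolytic. None of these is conditioning.

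At stake is the objective in the Introduction that the scent becomes a stand-alone cue. A positive within-arm gain, or similar gains in all four arms, could be published as an answer to that question when the data cannot supply one.

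**Working it through.** The plan gives no expected VAS gain, VAS SD or power figure for Phase 2, so there is no figure to reproduce. Effect sizes below are assumptions, in SDs of a participant's mean pre-post gain.

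**1. What each comparison identifies.** Let r = rest plus general expectation, b and l = direct effects of bergamot and lavender, g = generalised conditioning, s = stimulus-specific conditioning, e = extra expectation or familiarity for the trained scent. Assume that these add up and that s, g and e do not depend on the oil.

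| Group | Phase 2 oil | Expected VAS gain |
|---|---|---|
| 1 (match) | bergamot | r + b + g + s + e |
| 2 (match) | lavender | r + l + g + s + e |
| 5 (mismatch) | lavender | r + l + g |
| 6 (mismatch) | bergamot | r + b + g |
| 3, 4 | none | no session, no VAS |

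- Within-arm gain, Group 1: r + b + g + s + e. No term can be isolated.
- Within-arm gain, Group 6: r + b + g. A positive value does not imply g > 0.
- Pooled (1+2)/2 − (5+6)/2 = s + e. The terms r, b, l and g cancel because the oils are crossed.
- 1 − 5 = s + e + (b − l), and 2 − 6 = s + e + (l − b). The oil difference stays in.
- 1 − 6 = s + e, and 2 − 5 = s + e. The Phase 2 oil is held constant.

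The T2 MDBF scores of Groups 3 and 4 cannot supply r, because r is a change within a session.

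**2. Size of the within-arm problem.** Set all scent and conditioning terms to zero and leave a gain r. For a two-sided one-sample t test at 0.05 with n participants, the noncentrality is r√n. The planned arm size is 105 (2.11: 630 = 105 × 6), so the two match arms give n = 210. For r = 0.2, 0.2 × √210 = 2.90; for r = 0.3, 0.3 × √210 = 4.35. If 35% of 105 drop out, 105 × 0.65 ≈ 68 remain per arm and n = 136.

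| Assumed r | Match arms pooled, 2 × 105 | Pooled, 2 × 68 | One arm of 105 | One arm of 68 |
|---|---|---|---|---|
| 0.1 | 0.30 | 0.21 | 0.17 | 0.13 |
| 0.2 | 0.82 | 0.64 | 0.53 | 0.37 |
| 0.3 | 0.99 | 0.94 | 0.86 | 0.68 |
| 0.5 | 1.00 | 1.00 | 1.00 | 0.98 |

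Each entry is the probability of a significant gain with no scent effect.

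**3. Size of the problem between arms.** Simulation with no conditioning, r = 0.3, b = 0.1 and l = 0.4:

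- Pooled 1+2 vs 5+6 with e = 0: rejection about 0.05 at both 105 and 68 per arm, as it should be.
- 1 vs 5 with e = 0: rejection 0.59 at 105 per arm and 0.43 at 68. Here b − l = −0.3, so the error runs against conditioning. In 2 vs 6 the same 0.3 SD has the opposite sign and imitates conditioning.
- 1 vs 6 with e = 0: about 0.05.
- Pooled contrast with e = 0.1, 0.2, 0.3: rejection 0.17, 0.53, 0.88 at 105 per arm, and 0.13, 0.38, 0.70 at 68.

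**4. Reading the outcome patterns.**

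- Match > mismatch > 0 (pooled): supports a stimulus-specific part, subject to e. The gain left in the mismatch arms is unexplained.
- Match = mismatch > 0: r, b, l and g all fit.
- No gain in any arm: no sign of a response.

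**The case against.** The strongest reply is that the plan does not decide H2.1 on within-arm gains. Sections 2.9 and 2.13 make match versus mismatch the test, and under that rule equal gains would not support H2.1. This stands. A reader might infer that a quiet pause could explain the whole conditioning result, including match > mismatch. The documents do not support that: a common rest gain cancels between arms, and with crossed oils so do direct oil effects once the arms are pooled.

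A reader might also infer that nobody meets an oil unpaired with hypnosis. That is wrong for Groups 5 and 6, whose Phase 2 oil was never paired with hypnosis for them. What is missing is an arm inhaling an oil with no previous odour-hypnosis pairing at all.

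The Discussion admits that pharmacological effects of the oils may contribute to what is attributed to conditioning. This is a fair disclosure, but it does not cover rest or expectation and leaves the statements in 2.5.1, 2.7 and 2.9 unchanged. The reading in 2.9 is hedged, and its mention of context is broad. Even so, it does not name a direct oil effect or rest as an equal explanation.

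Finally, a reader might press the same criticism on Phase 1, where the models are to "see if there is a significant upward trend in pre-session relaxation over the 6 weeks for each group (learning effect". A trend within a group does not by itself show learning. However, Hypothesis 2.5 is exploratory and partly comparative, so this is a minor point and not part of the finding.

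**Conclusion.** The point holds in limited form. The within-arm Phase 2 VAS gain, and with it the first half of H2.1, does not identify a scent effect. Equal gains in match and mismatch arms do not identify generalisation. This follows from the layout of the arms and needs no numerical assumption. Its size does: with an assumed rest gain of 0.2–0.3 SD and no scent effect, the pooled match arms at 105 each would show a significant gain with probability about 0.82–0.99 (0.64–0.94 at 68 each).

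The test of stimulus specificity is sound against common rest gains and direct oil effects if it is pooled over the crossed oils or adjusted for the Phase 2 oil, under the additivity assumed above. It is not sound in the pairs 1 vs 5 and 2 vs 6. A familiarity or expectation difference remains even in the pooled contrast. Participants are not told the hypotheses (2.6), but the oils have distinct aromas (Introduction), so a switch is likely to be noticed. H2.1 is a secondary hypothesis; the primary efficacy analysis at T1 is unaffected.

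**What to change.** Change the wording in 2.7, 2.9, 2.10 and 2.13, and bring 2.5.1 and 2.6 into line:

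1. Rest the conditioning conclusion on the pooled, oil-balanced contrast (1+2 vs 5+6), or on a model adjusting for the Phase 2 oil. Do not draw it from 1 vs 5 or 2 vs 6 alone. Name familiarity or expectation as a remaining limitation.
2. Report within-arm pre-post VAS gains as descriptive, and remove the statements that they show an effect of the scent alone.
3. State that match = mismatch > 0 is inconclusive between generalised conditioning, direct oil effect, rest and expectation.

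These changes cost only text and need no new data.

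Optional: give Group 3 a scent-free timed pause in weeks 7–8, with VAS before and after, for comparison with Groups 1+2. The cost is platform prompts and participant time. It would control for rest only, leaving direct oil effects, the inhaler ritual and scent expectation mixed with conditioning. It would also end Group 3's role at T2 as the arm without further sessions, which 2.9 uses to judge residual benefit. That trade-off is for the investigators, and the wording changes do not depend on it.

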### Physiological subgroup

2.8

To complement self-reported outcomes with physiological data, the study includes an optional physiology component for a subset of participants. Up to 15 participants per group (approx. n≈90 total) who live in the Berlin/Brandenburg region will be invited to attend laboratory sessions at the Charité – Virchow Clinic Campus in Berlin. Electrophysiological measurements will be performed over a 15-min period during which the participant is at rest and in a supine position in the electrophysiological laboratory. During this period, the ECG and pulse are recorded using wearables. Electrophysiological measurements are to be recorded at two time points: initially at the baseline (T0) and subsequently following the six-week intervention period (T1). The ECG and pulse raw data indices were utilized to derive HRV and pulse wave variability (PWV), which are indices of autonomic nervous system (ANS) activity. The activity of the sympathetic nervous system (SNS), the parasympathetic nervous system (PNS), or both components of the ANS is indicated by these indices. In the course of each and every recording session, the participants were equipped with a Polar H10 chest-strap heart rate sensor (for the purpose of recording ECG for HRV) and a Polar Verity Sense optical pulse sensor (for the purpose of PWV via photoplethysmography). It is hypothesized that the response to the various 6-week interventions would be subject to change, and that the before-and-after effect would vary in the autonomous variables depending on the nature of the intervention. This methodology facilitates the representation of variation in dynamic changes across groups and over time. A comparison of the time points T0 and T1 will facilitate objective and quantitative mapping of the dynamic changes caused by the interventions. The autonomous measurements will facilitate the characterization of the interventions in terms of their mechanisms of action, and the extent to which each intervention leads to the assumed subjective improvement in relaxation/recovery (increased PNS). In addition, the study will elucidate the way this intervention enhances autonomic-vegetative function in the short term. The utilization of HRV and PWV in the time domain, in the frequency domain and nonlinear dynamics, has been demonstrated to be a reliable indicator of changes in sympathovagal balance (19). A greater HRV (particularly high-frequency HRV) and a slower PWV (which reflects vasodilation and reduced arterial stiffness) would suggest a shift towards parasympathetic dominance and relaxation. It is hypothesized that the combination of hypnosis and essential oils may result in increased relaxation, which is further enhanced by the intervention and over time from T0 to T1 in comparison to the hypnosis-only group. This is consistent with the hypothesis that deeper or more effective relaxation training is achieved through this method. The resultant phenomenon is evidenced by a decline in sympathetic tone and an augmentation in vagal tone, culminating in a state of profound relaxation and recuperation through the deactivation of the ANS.

However, given the small subgroup sample, these physiological analyses are exploratory. The measurements are carefully scheduled to avoid acute effects of a session (participants do not do a hypnosis session right before the measurement; it's a resting baseline capture). The present sub-study offers an objective evaluation of the intervention's impact on bodily stress arousal, in addition to its subjective effects.

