**Methods:**

This study protocol describes a randomized controlled trial evaluating the efficacy and conditioning potential of a digital self-hypnosis intervention combined with essential oil inhalation in adults with subsyndromal generalized anxiety. A total of *N* = 630 participants will be randomized into six groups. Four groups enter the primary efficacy analysis: (1) self-hypnosis + bergamot essential oil, (2) self-hypnosis + lavender essential oil, (3) self-hypnosis without essential oil, and (4) a minimal-intervention control. The intervention is delivered online over six weeks (Phase 1), followed by a two-week conditioning phase without hypnosis (Phase 2), in which stimulus-specific effects of the essential oils are tested. The primary outcome is subjective relaxation, measured by the Multidimensional Mood Questionnaire (MDBF) at baseline, post-intervention (6 weeks), and post-conditioning (8 weeks). Secondary outcomes include anxiety symptoms, perceived stress, sleep quality, well-being, and worry. In a voluntary subsample, heart rate variability (HRV) and pulse wave variability (PWV) will be assessed as physiological correlates of relaxation. In addition, the questionnaires are expanded to include open-ended questions, enabling an exploratory assessment of participants’ experiences, attitudes, and reflections on the intervention and its potential for sustainability. This approach complements quantitative results with qualitative insights and may reveal new perspectives for future research.

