**Figure 1 F1:**
[figure not shown]
Study overview and timeline. After online screening (GAD-7/PHQ-9), eligible participants are randomized (1:1:1:1:1:1) to six arms. Phase 1 (Acquisition; 6 weeks) involves self-hypnosis every ∼2 days, with or without essential oil exposure depending on group; pre/post-session relaxation is recorded via VAS. Phase 2 (Evocation; 2 weeks) tests conditioned responding: participants in aroma arms complete essential-oil exposure without hypnosis every ∼2 days (CS match = same oil as in Phase 1; CS mismatch = switched oil), with VAS recorded pre/post exposure. Assessments are conducted at baseline (T0), post-phase 1 (T1), and post-phase 2 (T2); follow-up surveys occur at 6 and 12 months without further application. An optional Berlin/Brandenburg subcohort undergoes exploratory physiological assessment (HRV, PWV) at the time points indicated. CS, conditioned stimulus; GAD-7, generalized anxiety disorder-7; PHQ-9, patient health questionnaire-9; HRV, heart rate variability; PWV, pulse wave variability; VAS, visual analogue scale.

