All groups 1, 2, 5, and 6 receive the full combined intervention (hypnosis + essential oil) in Phase 1, ensuring that Groups 5 and 6 have the same conditioning opportunity as their counterparts before the switch. Groups 3 and 4 allow us to isolate the effects of hypnosis itself (Group 3) and to account for any changes over time not attributable to the interventions (Group 4). Randomization is implemented via the SoSci Survey platform's built-in algorithm once participants are deemed eligible, ensuring allocation concealment. Because of the nature of the interventions, participants will know if they are using an oil or not (blinding is not feasible on the user level), but they will not be informed of the study hypotheses regarding which combination is expected to be most effective. The trial is single blinded in that the data analysts/statisticians will remain blind to group labels until after the primary analyses are completed, to prevent bias in outcome analysis.

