**Exploratory Hypothesis 2.3 (Moderators of Effect).** We will explore whether certain baseline factors moderate the intervention's effectiveness. Demographic factors like age, gender, or socioeconomic status might influence outcomes. For instance, it's possible that participants with higher initial anxiety, though still subthreshold, benefit more or less from the intervention, or that younger vs. older participants have different adherence rates. These analyses are exploratory and will be used to generate hypotheses for which subgroups respond best to this approach.

**Exploratory Hypothesis 2.4 (Physiological Effects).** We hypothesize that the combination of hypnosis and aromatherapy yields measurable physiological relaxation, reflected in increased parasympathetic activity or reduced sympathetic activity compared to hypnosis alone. In the laboratory subgroup, it is hypothesized that Group 1/2 (combined) will demonstrate larger increases in HRV, particularly high-frequency HRV, which is indicative of parasympathetic tone, and/or a greater reduction in heart rate and PWV from T0 to T1 than Group 3 (hypnosis only). This would suggest an additive effect of the essential oil on the body's relaxation response, consistent with objective evidence that an essential oil can modulate autonomic activity. However, given sample size limitations, this will be an exploratory outcome.

**Exploratory Hypothesis 2.5 (VAS Trajectory and Learning Effects).** By examining the VAS relaxation ratings collected before and after each session, we hypothesize that participants receiving the combined intervention will not only have larger acute relaxation gains per session on average than those in comparison groups, but they may also exhibit learning effects over time. A learning effect would manifest as gradually higher pre-session relaxation levels as weeks progress the participant's baseline state before each session improves, indicating they carry over some relaxed state or become more skilled at self-relaxation. We expect such effects might be most pronounced in those who undergo conditioning (Groups 1 and 2), potentially showing an upward drift in pre-session VAS scores and/or a plateau indicating habituation to relaxation. We will explore and graph these trajectories for insight into how the relaxation response develops with practice.

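### Entry to the optional HRV/PWV sub-study is not placed before allocation or arm disclosure, so the exploratory Groups 1/2 versus Group 3 physiology comparison is not shown to keep the protection of randomisation

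*Protocol article*

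**What the plan says.** Section 2.8 states that "the study includes an optional physiology component for a subset of participants", and the abstract calls it voluntary: "In a voluntary subsample, heart rate variability (HRV) and pulse wave variability (PWV) will be assessed as physiological correlates of relaxation". Its size is set by study group: "Up to 15 participants per group (approx. n≈90 total) who live in the Berlin/Brandenburg region will be invited to attend laboratory sessions". Recordings are made at T0 and T1.

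On allocation, section 2.6 says "Randomization is implemented via the SoSci Survey platform's built-in algorithm once participants are deemed eligible, ensuring allocation concealment". The Figure 1 caption gives the same order: "After online screening (GAD-7/PHQ-9), eligible participants are randomized (1:1:1:1:1:1) to six arms". Section 2.6 also concedes that "participants will know if they are using an oil or not (blinding is not feasible on the user level".

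Exploratory Hypothesis 2.4 in section 2.10 expects Groups 1/2 to show "larger increases in HRV, particularly high-frequency HRV, which is indicative of parasympathetic tone" than Group 3 from T0 to T1. Sections 2.8 and 2.10 label the physiology analysis exploratory, and the only reason given is small numbers. Section 2.8 nevertheless describes the T0–T1 changes as effects of the interventions and the sub-study as an objective evaluation of their impact.

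**The concern.** A comparison within a volunteer subset is still randomised if people volunteer before they are allocated, or at least before they know their arm. If they volunteer afterwards, the people who come to the laboratory from an oil arm may differ from those who come from the hypnosis-only arm in motivation, expectation or likely adherence. Attendance means two lab visits in a study that section 2.3 says is not remunerated, so the decision is not a trivial one.

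The hypothesised contrast, Groups 1/2 against Group 3, is between arms that participants can tell apart. The T0 recording adjusts for the starting level of HRV. It does not adjust for traits that influence the change over six weeks of self-directed practice. A difference in HRV change could then partly reflect who attended, and the article intends to read it as an added effect of the oil.

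The exploratory label does not cover this. Small numbers make an estimate imprecise, whereas arm-dependent entry makes it biased, and the article does not mention self-selection.

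**Working it through.** **1. The plan's own figure.** 15 per group × 6 groups = 90, which matches the stated total. Per arm this is 15/105 = 14.3% of the planned 105. The contrast in Hypothesis 2.4 has at most 15 + 15 = 30 participants (Groups 1 and 2) against 15 (Group 3).

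**2. Order of events.**
- Screening (sections 2.2 to 2.4) lists GAD-7, PHQ-9, treatment status, safety history and eligibility items. No question on willingness to attend the laboratory is listed.
- Randomisation follows once eligibility is established (section 2.6, Figure 1 caption).
- The oil kit is shipped (section 2.5.2), and the intervention starts the day after the baseline assessment (section 2.7). An oil-arm participant could hardly start on time unless allocated before T0. This is an inference.
- The first laboratory recording is at T0 (sections 2.7 and 2.8).
- The times of sub-study invitation, sub-study consent and arm disclosure are not stated.

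The natural reading is therefore allocation, then invitation by group, then voluntary acceptance.

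**3. Which contrasts are exposed.** Groups 1 and 5 have the same Phase 1 treatment, as do Groups 2 and 6. Arm-dependent opt-in therefore matters mainly between oil arms, hypnosis only and minimal intervention. That includes the hypothesised contrast.

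**4. Precision of the contrast** (unit SD, normal approximation). SE = √(1/30 + 1/15) = √0.1 = 0.316 SD. The difference detectable with 80% power is (1.960 + 0.842) × 0.316 = 0.89 SD. At d = 0.35, 0.40 and 0.50, power is about 0.20, 0.24 and 0.35. The first two are the planning range in section 2.11 for the questionnaire outcome and serve here only as a yardstick.

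**5. Illustration of the mechanism.** The documents give no uptake by arm and no HRV variance, so the model parameters are assumptions.
- Unmeasured trait U ~ N(0,1). Probability of opting in: logit p = −1 + bU, with slope b allowed to differ by arm.
- HRV change in SD units: Y = ρU + √(1 − ρ²)·e, with no treatment effect.
- Bias = mean Y among oil-arm volunteers minus mean Y among Group 3 volunteers.
- Two-sided type I error = 1 − Φ(1.96 − bias/0.316) + Φ(−1.96 − bias/0.316).

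| b (oil arms) | b (Group 3) | ρ = 0.2: bias, type I | ρ = 0.3: bias, type I | ρ = 0.5: bias, type I |
|---|---|---|---|---|
| 0.5 | 0.5 | 0.00, 0.050 | 0.00, 0.050 | 0.00, 0.050 |
| 0.5 | 0 | 0.07, 0.055 | 0.11, 0.063 | 0.17, 0.086 |
| 1 | 0 | 0.12, 0.066 | 0.18, 0.086 | 0.30, 0.155 |
| 1 | −0.5 | 0.19, 0.090 | 0.28, 0.144 | 0.47, 0.315 |

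Example: 0.467/0.316 = 1.48. The upper tail is 1 − Φ(0.48) ≈ 0.315 and the lower tail is negligible. Exchanging the slopes between arms reverses the sign of the bias.

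**The case against.** The strongest objection is that the timing is inferred. The article does not say that participants opt in after learning their arm, and a condensed article may leave the consent sequence to the full protocol. A cap per group does not settle the matter either. The study team can apply it to people who volunteered at screening, and the remedy proposed here also gives 15 per arm. Both points stand. A reader might infer that participants do choose attendance knowing their arm, or that the cap itself breaks randomisation. The documents support neither as fact.

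The direction is also open. Enthusiasts might be over-represented in the oil arms. Equally, only the most motivated might come from Group 3, which would work against Hypothesis 2.4. The documents do not show a bias in favour of the oil.

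Finally, the analysis is exploratory, has little power and leaves the questionnaire outcomes untouched. This limits the consequence.

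The objection does not remove the point. The article states an invitation rule by study group, open-label arms and randomisation at eligibility, and then puts a causal reading on the result. On what it states, nothing protects that reading from arm-dependent entry, and the reason given for the exploratory label does not disclose the risk.

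**Conclusion.** The point holds in a limited form. The exploratory T0–T1 HRV/PWV comparison of Groups 1/2 with Group 3 may lose, and is not shown to keep, the protection of randomisation. It would be too strong to say that the protection is lost, because the times of sub-study consent and arm disclosure are not stated.

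The size is unknown. It is zero if opt-in does not depend on the arm. Under the assumed opt-in slopes and correlations it runs from about 0.07 to 0.47 SD in absolute value, in either direction. The upper end exceeds the planning effect of d about 0.35–0.40. These figures show what the mechanism can do and do not estimate what will happen in this trial. The primary outcome and the other questionnaire outcomes are unaffected. The change is worth making before enrolment, because selection into the subset cannot be undone afterwards.

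**What to change.** Preferred: record Berlin/Brandenburg residence and consent to both laboratory visits in the screening survey, before randomisation. Randomise those who consent as their own stratum, for example in blocks of six up to 90, which gives 90/6 = 15 per arm. Reword the invitation sentence in section 2.8 accordingly.

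Minimum: take sub-study consent before the arm is disclosed and say so in section 2.8. If this is already the practice, one sentence settles the matter.

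If neither is feasible: report uptake and baseline characteristics of the sub-study by arm, describe the physiology comparison as non-randomised, and remove the wording in section 2.8 that attributes the T0–T1 changes causally to the interventions.

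Cost: sub-study consent is taken slightly earlier, with an added screening item and a second randomisation list. No extra participants, visits or staff are needed. The article mentions only the survey platform's built-in algorithm, so whether it supports a separate blocked stratum has to be checked.
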